## Abstract

**Background:**

In patients treated with oral anticoagulants, subcutaneous injections of anti-tetanus vaccine are usually recommended to reduce the risk of bleeding, although the effectiveness of the vaccine has only been proven for intramuscular injection. The objective of this study was to compare the safety and efficacy of intramuscular and subcutaneous injections of tetanus-diphtheria vaccine in patients treated with oral anticoagulants.

**Methods/design:**

We present a prospective, double blinded, clinical trial comparing two groups of patients with oral anticoagulants: one group was administered tetanus-diphtheria vaccine by intramuscular injection, while the other was administered the same vaccine by subcutaneous injection. Allocation to each group was randomized and the duration of the study was six years.

Study population: all patients treated with oral anticoagulants, who had been administered with at least one dose of vaccine, at 15 Health Centres in Vigo (Spain), and who agreed to participate in the study. The sample size was 115 patients in each group. The main variables for the safety analysis were the measurement of the brachial diameter, the appearance of basic injuries at the vaccine administration site, the appearance of pain and systemic reactions. The variable used for the efficacy analysis was a significant increase in the titres of anti-tetanus toxoid antibodies.

An Intention-to-treat analysis will be performed. Details will be classified according to the administration route, while within each group a 3-tiered stratification will be defined by the administered number of doses. As a measure of association, relative risk will be estimated; the reduction of relative risk will also measured. For safety and to control the confounder effect, a logistic regression analysis will be carried out. As a measure of impact the reduction of absolute risk in relation to the total number of patients to be treated and the Number Needed to Treat will be estimated.

CONSORT 2010 guidelines were applied for reporting parallel group randomised trials.

**Discussion:**

The most significant difficulties on the project are related to the large number of participating centres, required to obtain a viable study population sample size, and the coordination given the scattering of the centres and researchers.

**Trial registration:**

ISRCTN69942081.

## Background

Despite its low incidence, tetanus is a major public health problem with a high fatality rate (40-50%) [1]. The annual register of cases has slowly been descending over the last 10 years, with an average of 25 cases/year in Spain (incidence of 0.06 cases per 100,000 population) [1]. In Galicia (Spain) during the last 5 years, on average, there have been 3 cases reported per year [2].

Tetanus is a disease that can be fully controlled, as it can be prevented by vaccination. However, it cannot be eradicated, because *Clostridium tetani* is a widely distributed microorganism in the environment. Immunization is highly effective [1], providing long-term protection and is recommended for the whole population in general, even though booster doses are required to maintain immunity, after the first vaccination [3].

Most cases of tetanus occur in previously unvaccinated adults, especially among those over 60 years of age [4]. Seroprevalence studies demonstrate that immunity from tetanus is higher than 95% in Spanish cohorts born after 1982, decreasing progressively in cohorts born prior to this date; for example, in the 1957–1966 cohort immunity is only around 55% [1]. Studies of the elderly have reported seroprevalence of 7.7% in those over 70 years of age [5]. In Spain, the fact that most adults of over 50 years of age have not been vaccinated or have only been incompletely vaccinated is probably because the immunization calendar for the five-dose course of tetanus vaccine was not introduced until the early 1970s [6].

With any wound, the need to administer active immunization (tetanus toxoid) alone or jointly with passive immunization (tetanus immunoglobulin) depends on the type of wound, the probability of contamination with tetanus bacillus, and also on the knowledge of the patient’s vaccination history [1]. The current recommended treatment is the combined tetanus-diphtheria vaccine (presentation for adults) or intramuscular Td vaccine [1–3].

Most anticoagulated patients in primary care consultations are seen due to auricular fibrillation and, on average, they are over 56 years of age [7, 8]. Hence, vaccination coverage is probably low [9].

In anticoagulated patients, because of the hypothetical risk of bleeding after injection, use of the intramuscular route has been traditionally discouraged, with the subcutaneous route being recommended, even for vaccines that are routinely administered intramuscularly, as for tetanus [10–12]. Indeed, in the literature, a few cases of major bleeding complications have been published [13]. Yet, although there is no uniformity of results in studies comparing the effectiveness of the two routes [14, 15], vaccine efficacy studies have used the intramuscular route [1, 10, 14], and subcutaneous administration may be less effective compared to intramuscular administration. Moreover, for most vaccines, local adverse reactions are more frequent with subcutaneous administration than with the intramuscular route [14–16].

The safety of the intramuscular route for the hepatitis B [17] and influenza vaccines [18], which are also administered intramuscularly, has been demonstrated in patients with alterations in coagulation and, consequently, the 2006 CDC guidelines recommend intramuscular injection for the tetanus-diphtheria (Td) vaccine depending on medical criteria [10].

We have not found any study in the literature that assesses the safety and efficacy of intramuscular (IM) and subcutaneous (SC) administration for the Td vaccine in patients treated with oral anticoagulants.

The objective of this study was to compare the safety and efficacy of the intramuscular and subcutaneous routes of administration for tetanus-diphtheria (Td) vaccine in patients treated with oral anticoagulants, and to verify the hypothesis that IM administration is safer and has greater efficacy.

## Methods/design

We present a prospective, double-blind, phase IV clinical trial with two parallel groups and layered randomized assignment. Each one of these parallel groups was given doses of the corresponding tetanus vaccine, either intramuscularly (Group 1) or subcutaneously (Group 2), as shown in Figure 1. The layers were defined by the number of doses of the corresponding anti-tetanus injections (one, two or three), in each tier. This trial was only designed for the vaccination of the general anticoagulated population, and not for situations with wounds.

**Figure 1 Fig1:**
[figure not shown]
**Summary of trial design.**

### Patients

The following inclusion criteria were applied to all patients who were undergoing monitored treatment with oral anticoagulants at 15 Health Centres within the Vigo Primary Care Area.

### Inclusion criteria

 Patients treated with oral anticoagulants, for whom administering of at least one dose of anti-tetanus vaccine was indicated. This criterion was for those patients whose vaccination status was unknown, uncertain, or if they were clearly not vaccinated.  After being duly informed of the nature of the trial, patients were included if they gave written consent to be vaccinated and participate in the study.

### Exclusion criteria

  Severe local reaction to previous doses with the whole circumference of the injected limb being affected.  Peripheral neurological disorders due to previous doses.  Severe anaphylactic reaction due to previous doses or any of the components.  Poor haematological control (International Normalized Ratio [INR] > 4) in the last 2 months.  Serious illness, terminal stages of diseases, immobilized, adversely affected by chronic pathology or immunosuppressive states.  Pregnant or breast-feeding women.

### Sample size

Assuming that for the IM route the percentage of local side effects is 30% [11, 15, 16] and expecting an increase of 18% [15] in local secondary effects for the alternative route (SC), using a bilateral approach, with a 95% confidence interval, a beta risk of 0.20 requires 115 patients in each group. Taking into account the possible 15% loss in information, the final sample size was 135 patients in each group. With this sample size, it was estimated that a 3 UI/ml mean difference in antibody levels could be detected.

### Interventions

Patients were recruited at the primary care centres by their family doctors. During the first visit, the doctor assessed the vaccination state of the patient, taking into account the vaccination records in the patient’s medical history, or by interviewing the patient if such information was not available. According to the number of doses received and the date of the last dose, the doctor was able to determine if the patient was properly vaccinated (and, if so, the patient was excluded from the study), or whether they needed to be given a booster dose, or to start or complete adult primo-vaccination. The guidelines used for applicable vaccination were those recommended by the Spanish Ministry of Health in 2008 [1, 3, 4]:

For complete primo-vaccination, and less than 10 years since the last dose: nothing (not included in the study).For complete primo-vaccination, and more than 10 years since the last dose: 1 booster dose.In cases of no previous vaccination: complete primo-vaccination with three doses separated by 1–2 months between the first two, and 6–12 months between the second and third, with subsequent booster doses every 10 years. If primo-vaccination had been started prior to the beginning of the study, the patient was administered doses according to the standard schedule.In cases of incomplete primo-vaccination: One dose if the patient already had been administered two doses, and the last dose was more than a year earlier.Two doses, separated by six months, if the patient had one dose administered more than a month earlier.

When vaccination status was unknown or doubtful, primo-vaccination was started.

After assessing if the patient fulfilled all inclusion criteria, and none of the exclusion criteria, they were invited to participate in the study and, if they agreed to sign informed consent, were included in one of the tiers, according to the corresponding (allocation ratio 1:1) vaccine dose (one, two or three). The patients were given an appointment to have an INR test and, if the score was less than 4, a blood sample was taken to determine anti-tetanus antibodies, and a dose of vaccine was immediately administered, so that the patient could proceed to the corresponding nursing consultancy. The nurse was responsible for requesting from the randomization centre, by telephone, the administration route to which the patient had been assigned*.* The patient was not informed of the administration route used*.* Patients requiring more than one dose received all doses via the same route, and were given appointments in relation to the interval and number of corresponding doses.

The doctor was blinded to the administration route and also to the follow-up appointments (1, 2, 14 and 30 days) after each dose of the vaccine to detect any side effects.

On the first visit, after administering the vaccine, and at 30 days after the last dose of anti-tetanus vaccine (ATV), the antibody titre was determined for all patients using enzymatic immunoanalysis.

The systematic physical examination at each visit included the following aspects:

 General appearance. Temperature Arterial blood pressure. Measurement of the brachial perimeter at the height of the deltoid on the first visit, and at the site of inoculation after vaccination. Examination and palpation of the injection site looking for basic injuries. Homolateral axillary palpation of the injection site. Any examination required due to the emergence of a general and/or unexpected side effect.

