### Variables

The main analytical safety variables were:Measurement of the brachial perimeter in centimetres.Appearance of basic injuries (redness, swelling, heat, granulomas, haematoma) in the area of administration of the vaccine, axillary nodes, and the appearance of pain measured with the visual analogue pain scale.The emergence of general symptoms (fever, malaise, headache, weakness, arthralgias).The appearance of any serious adverse effect: one that was fatal or posed danger to patient’ life, ended in disabilities or required hospitalization.

For each route of administration, the main variable used in the efficacy analysis was the increase in anti-tetanus antibodies following vaccination.

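### Brachial perimeter has one landmark at the first visit and another after vaccination, and the protocol does not say that they coincide or are the same for both routes

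*Protocol article*

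**What the plan says.** The list of examination items in the Interventions section gives the measuring rule: "Measurement of the brachial perimeter at the height of the deltoid on the first visit, and at the site of inoculation after vaccination". The examination is repeated at each visit, and the same section sets "follow-up appointments (1, 2, 14 and 30 days) after each dose of the vaccine to detect any side effects".

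The Variables section opens the main safety variables with "Measurement of the brachial perimeter in centimetres". It does not say whether the analysed quantity is the post-dose value or a change from the first visit. The abstract describes the variable differently, as "the measurement of the brachial diameter".

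The injection site is not named. The nearest indication is another examination item, "Homolateral axillary palpation of the injection site", which places the injection on an upper limb but gives no level.

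The Statistical analysis section compares quantitative variables between groups with Student's t test, or Mann–Whitney if its conditions fail, and uses a paired t test for paired quantitative variables. Perimeter is not named under either. The only covariate-adjusted model is a logistic regression for safety, which does not suit a measurement in centimetres.

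**The concern.** Arm circumference varies along the arm. If the tape goes round the arm at one level before vaccination and at another afterwards, the two readings differ even without swelling. Within an arm of the trial, that difference would be read as swelling or shrinkage.

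Between routes the question is narrower: does the measuring level depend on the route? After vaccination the level follows the inoculation site. If subcutaneous and intramuscular injections were given at different heights, the measuring level would differ by randomised group. Randomisation would not remove this, because it would be a consequence of the assigned route. The trial exists because of feared bleeding after intramuscular injection, and perimeter is the local safety variable recorded in centimetres, so a bias here would bear on the main safety question.

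A lesser matter is the age of the reference. The rule provides for a reading at the first visit and none immediately before dose 2 or dose 3.

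**Working it through.** **The plan's own figure first.** The sample size rests on local side effects, 30% (IM) against 30 + 18 = 48% (SC), two-sided alpha 0.05, power 0.80. With mean proportion 0.39:

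n = [1.960·√(2·0.39·0.61) + 0.842·√(0.30·0.70 + 0.48·0.52)]² / 0.18² = (1.352 + 0.571)² / 0.0324 ≈ 114.1, rounded up to 115.

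This reproduces the stated 115. For loss, 115/0.85 = 135.3, against the stated 135. Perimeter does not enter, so this point does not touch the sample size.

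**What a difference in level does.** For route r and follow-up time t, write the post-dose reading minus the first-visit reading as S_r(t) + L_r. Here S is true swelling and L is the difference due to measuring level alone.

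- Within an arm, the paired change estimates S_r + L_r. It is biased whenever L_r is not zero, even if L is the same in both arms.
- Between routes, the difference is (S_IM − S_SC) + (L_IM − L_SC). If L is the same in both arms it cancels. Only a route-dependent level biases the comparison.
- The between-route result does not depend on using a change score. Raw post-dose perimeters are also taken at the inoculation site, so a route-dependent level would enter them too.
- Adjusting for the first-visit perimeter removes variation between patients in arm size. It does not remove L_IM − L_SC.

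**Illustrative size.** The documents give neither an offset nor an SD, so both are assumed. Let b = L_IM − L_SC, with 115 per arm and SE = SD·√(2/115). The false-positive rate of a two-sided 0.05 test with no true difference in swelling is 1 − Φ(1.96 − b/SE) + Φ(−1.96 − b/SE).

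| Assumed SD of change (cm) | b = 0 | b = 0.25 cm | b = 0.5 cm |
|---|---|---|---|
| 1.0 | 0.05 | 0.47 | 0.97 |
| 1.5 | 0.05 | 0.24 | 0.72 |
| 2.0 | 0.05 | 0.16 | 0.47 |

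Example: SD 1.5 gives SE = 1.5 × 0.1319 = 0.198. With b = 0.25, b/SE = 1.26 and the rate is about 0.24. The b = 0 column applies if the levels coincide or differ equally in both arms.

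**Age of the first-visit reading.** In the three-dose schedule (Interventions), dose 2 comes 1–2 months after dose 1 and dose 3 comes 6–12 months after dose 2. Dose 3 is therefore 1 + 6 = 7 to 2 + 12 = 14 months after dose 1. In the two-dose schedule the doses are six months apart. Across doses 2 and 3 the reference is about 1 to 14 months old.

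**A day-30 reference.** Subtracting the same-site day-30 value gives S_r(t) − S_r(30). The level term cancels, but the between-route contrast becomes [S_IM(t) − S_SC(t)] − [S_IM(30) − S_SC(30)]. If residual swelling at day 30 differs by route, part of the effect is subtracted.

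**Naming.** For a circular arm, perimeter is about 3.14 times diameter, so the abstract and the Variables section describe different quantities.

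**The case against.** The strongest reply is that the rule describes one level in two ways. Before vaccination there is no inoculation site, so the baseline needs an anatomical landmark; afterwards the site itself can be named. This is a natural reading and the text does not exclude it. It stands against anyone who infers that the recorded change does mix swelling with level. The documents do not support that, because the site is never named.

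A route-specific site also sits badly with the masking. The examining doctor is blinded to route and palpates the injection site, and the Discussion stresses keeping doctors and patients blind. That makes a common site plausible, and a common offset cancels between routes. It is an inference, though, and one sentence would settle it.

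Arm-size drift over months is not shown to differ between randomised groups, so the old reference mainly adds noise. A day-30 reading after the previous dose also exists. In the three-dose schedule it is at most about 1 month old at dose 2 (2 − 1), but 5 to 11 months old at dose 3 (6 − 1 to 12 − 1).

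Measurement detail may lie in the full protocol, and researchers attended a workshop on measuring the study variables. But the article itself states a rule with two landmarks. The workshop preceded the study, while approvals after the first inclusion in January 2009 took the centres from 6 to 15. That does not show later centres were untrained, only that an unwritten convention is a weak safeguard.

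Finally, swelling and haematoma are recorded separately, so the local safety assessment does not hang on perimeter alone. That stands.

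**Conclusion.** The point holds as a defect of definition with a conditional consequence. A main safety variable has two landmarks that are not stated to coincide or to be common to both routes. A within-arm change could include a change of level; the between-route comparison is biased only if the injection level differs by route.

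No size can be taken from the documents. Under the assumed SDs of 1.0 to 2.0 cm, a route-dependent offset of 0.25 cm gives a false-positive rate of about 0.16 to 0.47, and 0.5 cm gives 0.47 to 0.97. If the level is common to both routes, the rate stays at 0.05.

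The 1- to 14-month-old reference for doses 2 and 3 is mainly a loss of precision. A reader might take it as a further bias between routes, but nothing shown supports that. The planned sample size is unaffected. The diameter/perimeter conflict is a plain inconsistency in naming.

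**What to change.** **Measurement.** State one fixed, marked level on the injected arm, the same for both routes. Read the perimeter there before each dose and at each follow-up visit.

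**Analysis.** Compare routes on post-dose perimeter adjusted for the pre-dose value (ANCOVA), in place of the unadjusted t or Mann–Whitney test.

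**Data already collected.** Adjust for the first-visit perimeter, which costs nothing because it was recorded. This gains precision but cannot remove a route-dependent level, so also report the injection level by route. If the level was the same, that statement closes the between-route question. Use the same-site day-30 value as reference only in a sensitivity analysis: it is post-treatment, could subtract part of a route effect, and loses patients without that visit.

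**Wording.** Write perimeter instead of diameter in the abstract.

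**Cost.** One sentence in the measuring instructions, one extra tape reading before doses 2 and 3, and a change of analysis wording. The sample size does not change.

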### Laboratory analysis

  Determination of INR through the capillary technique with a reflectometer.  Determination of antitoxoid tetanus antibodies by enzymatic immunoanalysis in a centralized Laboratory (Barcelona).

### Data collection

The first patient was included in January 2009, with an initial 24-month forecast for the period of inclusion, which subsequently had to be extended to 72 months, due to difficulties in reaching the predetermined sample size

All data were recorded on a case report form (CRF) designed for that purpose. A specific database was created to upload the data.

A training workshop was held for all researchers participating in the clinical trial regarding techniques, collection of data and measurement of study variables prior to the beginning of the study.

### Premature abandonment by a patient

The researcher determined the primary reason for premature abandonment by the patient and recorded this information on the CRF. Patients could be prematurely removed from the study for one of the following reasons: side effects in primo-vaccination; patient withdrew consent; loss of follow-up; administrative problems or death.

For patients who could not be contacted and missed the follow-up, the researcher documented the steps taken to contact the patient.

### Variables

The main analytical safety variables were:Measurement of the brachial perimeter in centimetres.Appearance of basic injuries (redness, swelling, heat, granulomas, haematoma) in the area of administration of the vaccine, axillary nodes, and the appearance of pain measured with the visual analogue pain scale.The emergence of general symptoms (fever, malaise, headache, weakness, arthralgias).The appearance of any serious adverse effect: one that was fatal or posed danger to patient’ life, ended in disabilities or required hospitalization.

For each route of administration, the main variable used in the efficacy analysis was the increase in anti-tetanus antibodies following vaccination.

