### Statistical analysis

Descriptive, statistical analysis will be used to classify the data into two groups, according to the route of administration, while within each group a 3-tiered stratification will be defined by the administered number of doses. The quantitative data will be summarized by estimating the arithmetic mean and median as measures of central tendency, as well as the standard deviation as a measure of dispersion. For qualitative variables, proportions with 95% confidence intervals will be estimated.

After checking the conditions of application and assuming an alpha error of 0.05, the Chi-squared test will be used to determine the statistical differences between the qualitative variables in the two study groups. Prior checking of all the criteria for application will be carried out before the Student’s-t test (0.05 alpha) is used to examine the levels of significance in the differences in quantitative variables for independent data. If the conditions of application were not met, the non-parametric Mann–Whitney U test will be used. The Student’s t test for paired data will be employed for paired quantitative variables.

As an association measurement, relative risk will be estimated with a 95% confidence limit, according to the method of Mantel and Fleiss. In addition, as a further association measurement, relative risk reduction will be calculated with a 95% confidence interval. For the safety study and to control the effect of different confounding covariables, a logistic regression analysis will be simultaneously performed.

As a measurement of impact, the reduction of absolute risk (RAR) and the Number of patients Needed to be Treated (NNT) to prevent an event will be calculated with 95% confidence intervals.

An Intention-to-treat (ITT) analysis will be carried out, even when it was highly or totally improbable that crossing occurs within groups, because this intervention is predictably limited to a particular moment.

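### No single primary safety outcome is defined to match the local-side-effect percentage on which the sample size rests

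*Protocol article*

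**What the plan says.** All references are to the protocol article.

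- **Sample size.** One binary outcome is used: "Assuming that for the IM route the percentage of local side effects is 30"%, with an increase of 18% "in local secondary effects for the alternative route (SC"), the subcutaneous route. The error rates are set "using a bilateral approach, with a 95% confidence interval", and "a beta risk of 0.20 requires 115 patients in each group".
- **Variables.** The list introduced by "The main analytical safety variables were" has four headings: (1) brachial perimeter; (2) five kinds of injection-site lesion, axillary nodes and pain on a visual analogue scale; (3) five general symptoms; (4) serious adverse effects. The main efficacy variable is the increase in anti-tetanus antibodies.
- **Statistical analysis.** For qualitative variables, "assuming an alpha error of 0.05, the Chi-squared test will be used". For quantitative variables the t test is used, also at 0.05, or the Mann-Whitney test. Tests are assigned by type of data. No variable is put first and no order is given.
- **Background.** The trial is meant "to verify the hypothesis that IM administration is safer and has greater efficacy". The Discussion words the safety aim differently, as showing that IM is safe.

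**The concern.** The power calculation and the list of main variables should point to the same outcome, and here they do not. The calculation needs a yes/no result per patient. The article does not say which items make a patient a case, what pain score counts, or over which visits and doses. The Statistical analysis section also promises relative risks, absolute risk reductions, numbers needed to treat and a logistic regression for safety. All of these need a defined event, and none is named.

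The stated hypothesis is confirmatory. With several variables all called main and no rule for choosing among them, the plan does not prevent a claim that IM is safer from resting on whichever item reaches significance. The comparison that was actually powered could then become one result among many.

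**Working it through.** **1. Inputs.** From Sample size: 30% on IM, an increase of 18%, two-sided 0.05, 80% power, 15% loss. From Variables: the list of safety variables. From Statistical analysis: 0.05 per test. Correlations between test statistics are not in the article and are assumed below.

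**2. Reproducing the plan's figure.** Read the 18% as percentage points (30% v 48%) and use pooled variance without continuity correction:

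n = [1.96 × √(2 × 0.39 × 0.61) + 0.8416 × √(0.30 × 0.70 + 0.48 × 0.52)]² / 0.18²
= (1.352 + 0.571)² / 0.0324 ≈ 114.1, rounded up to **115 per group**.

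This matches the article, and power at 115 is 80.3%. Read as a relative increase (30% v 35.4%), the same formula gives 1184, so percentage points are meant. For losses, 115 / 0.85 = 135.3, in line with the stated 135. The arithmetic is sound, and it covers one test of one binary outcome at 0.05.

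**3. Counting the main safety variables.** By heading there are 4. By named item: perimeter 1 + site lesions 5 + nodes 1 + pain 1 + general symptoms 5 + serious adverse effects 1 = 14.

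**4. Chance of at least one false-positive safety difference, each test at two-sided 0.05.** Under independence:

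- either direction: 1 − 0.95^4 = 18.5%; 1 − 0.95^14 = 51.2%
- favouring IM only: 1 − 0.975^4 = 9.6%; 1 − 0.975^14 = 29.8%

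With correlation, from a simulation of equally correlated normal test statistics (300,000 draws, cut-off 1.96):

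| Tests | Assumed correlation | Either direction | Favouring IM |
|---|---|---|---|
| 4 | 0 | 18.5% | 9.6% |
| 4 | 0.5 | 15.6% | 7.7% |
| 4 | 0.8 | 11.3% | 5.7% |
| 14 | 0 | 51.2% | 29.8% |
| 14 | 0.5 | 34.7% | 17.4% |
| 14 | 0.8 | 19.7% | 9.8% |

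A single two-sided test allows 5% in either direction and 2.5% in favour of IM. Every row exceeds both.

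**5. Keeping every variable main with a Bonferroni split.** For the same 30% v 48% comparison:

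- 4 tests, alpha 0.05/4 = 0.0125: 163 per group needed; power at 115 is 62%.
- 14 tests, alpha 0.05/14 = 0.00357: 206 per group needed; power at 115 is 45%.

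**6. One named primary safety outcome.** Alpha stays at 0.05, the sample size at 115 and power at about 80%, provided the 30% and 48% refer to the composite as it is then defined.

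**The case against.** - **Local reactions are listed.** This stands. The second heading in Variables holds site lesions, nodes and pain, apart from general symptoms, and plausibly corresponds to the local side effects of the sample size. A reader might infer that the powered outcome is absent from the list, or that the power belongs to no listed variable. The text does not support that: the components are there. What is missing is their designation and definition as one patient-level outcome.
- **Testing at each visit is not planned.** This also stands. The Interventions section schedules checks at 1, 2, 14 and 30 days after each dose, and a reader might infer a test at each. No section says so, and the figures above do not count visits. Nor does the article say whether headings or items are the unit of testing, or that one significant item would suffice. It simply does not rule that out.
- **The independence figures are ceilings.** Correct. Signs at one injection site are likely to be correlated, and if some items are rare (no rates are given) their tests would run below 0.05. Taking 51% as the rate of false claims that IM is safer would be wrong, because it also counts errors that favour the subcutaneous route.
- **Multiplicity may be handled in an analysis plan not shown.** Fair, so a missing adjustment is not the point. Choosing the primary outcome and matching it to the sample size is protocol content. The article addresses both, and they do not agree.
- **The plan also estimates effects with 95% intervals.** True, but Background still states a hypothesis to be verified.

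**Conclusion.** The point holds in limited form. The trial is powered for the percentage of patients with local side effects, but that percentage is neither defined as one outcome nor designated to decide the safety claim. Four headings, or 14 items, share the status of main variable at 0.05 each.

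The chance of at least one false-positive safety difference in either direction is about 11-19% for 4 tests and 20-51% for 14, for assumed correlations from 0.8 down to 0. Counting only errors that favour IM, it is about 8-10% and 17-30% for correlations from 0.5 down to 0, against 2.5% for a single two-sided test. At correlation 0.8 the IM-favouring figures fall to about 6% and 10%, still above 2.5%.

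The existence of the mismatch is certain from the text. Its size is not, because it depends on the unit of testing and on correlations that the article does not give. The sample-size arithmetic itself is not at fault. Whether the safety aim is safer (Background) or safe (Discussion) also needs to be reconciled.

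**What to change.** The analyses are described in the future tense and the route is masked to the analysts, so these changes can be made before unblinding:

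1. Name any local reaction, yes/no per patient, over a stated follow-up window, as the single primary safety outcome. Build it from the local items already in Variables and state which items count and what pain score qualifies. The sample size stays at 115 per group before losses, with about 80% power.
2. Keep the increase in anti-tetanus antibodies as the single primary efficacy outcome, for example the 30-day titre adjusted for baseline.
3. Claim that IM is safer and more efficacious only if both are significant at 0.05 in its favour. No alpha split is needed.
4. Report the other safety variables as secondary with 95% confidence intervals. Show haematoma separately: bleeding is the reason the article gives for avoiding IM, and a composite could hide more haematomas behind fewer mild reactions.

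**Cost.** Individual symptoms lose confirmatory status. Joint power is lower than either single power: if each outcome had 80% and they were independent, 0.80 × 0.80 = 64%. The true figure is unknown, because the article gives a detectable difference of 3 UI/ml for antibodies without a standard deviation or power. No extra patients are needed for the safety comparison.
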